## **PATIENT SYMPTOMS AND QUALITY OF LIFE**

### **Assessment of Symptoms**

Clinical symptoms will be assessed by the COPD activity test (CAT) at each visit.

The possible improvement in dyspnoea will be assessed via the Baseline and Transition Dyspnoea Index (BDI/TDI) after each treatment phase. The BDI/TDI provides a multidimensional measurement of dyspnea based on 3 components that evoke dyspnea in activities of daily living, in symptomatic COPD patients.

### **Quality of life**

Quality of life measures were made using the St George's respiratory Quality of Life Questionnaire. Self-completed questionnaires were performed before and after each treatment phase. A clinically relevant change was considered to be 4 for total score. End-points included the global score change during active and placebo phases, as well as scores for the sub-scales of symptoms, activity and impact.

### **Ease of expectoration**

Patients were asked to report their subjective view of the sputum ease of expectoration using a visual analogue scale after sputum expectoration as described. (25). This data was collected at all visits.

**Patient diary**

Patients are advised to keep a diary the study. Data will be included into a paper diary. Concomitant medication and adverse event will be recorded in the diary daily.

**6.3. REPLACEMENT OF DROP-OUTS AND WITHDRAWALS**

It will be documented whether or not each patient completed the clinical study. If for any patient either study treatment were discontinued the reason will be recorded. Patients terminating the study prematurely will not be replaced. An estimation of 4 patients dropping out of the study has been considered when determining the number of patients to be recruited.

**7 ASSESSMENT OF EFFICACY AND SAFETY****7.1. ASSESSMENT OF EFFICACY****7.1.1. PRIMARY EFFICACY VARIABLE**

The primary endpoint is sputum weight after 3 weeks of Tylaxopol and that after 3 weeks of saline treatment which will be analyzed for the Per Protocol Population. Estimated differences will be presented together with 95% confidence intervals (CIs) for the difference and two-sided p-values from a corresponding t-test. This analysis will be repeated for the ITT Population.

### 7.1.2. **SECONDARY EFFICACY VARIABLES**

Secondary endpoints: The analysis of symptom scores ((CAT, BDI and TDI), ease of sputum production by analog scale, lung function parameter (FVC, FEV1, MEF25, RV, RV/TLC), will use the same methodology as that for the primary endpoint, using the ITT population. The analysis will include Day 1 and week 3 data. In addition acute changes of sputum weight on Day 1 at each treatment arm will be analyzed as described for the primary parameter.

Other Endpoints: Biomarker profiles (sputum cells, IL-1, IL-6, IL-8), in sputum and serum (IL-6, LBP, CRP) will be analyzed using an analysis of covariance (ANCOVA) model with covariates of baseline, smoking status and treatment. Estimated treatment differences along with corresponding 95 % CIs will be presented for the treatment comparison

### 7.2. **ASSESSMENT OF SAFETY**

Safety assessments will consist of monitoring and recording all adverse events and serious adverse events, the regular monitoring of hematology, regular measurement of vital signs and the performance of physical examinations.

### 7.3. **LABORATORY ASSESSMENTS**

#### 7.3.1. **SPUTUM PROCESSING**

Induced sputum will be analyzed for cell differentiation, as well as protein levels of cytokines.

Sputum will be sampled and processed as follows:

Subjects first inhale 200 µg Salbutamol and consecutively nebulised the study medication. During this procedure, it will be important to flush and clean the nose for disposal of lower part of squamous epithelium cells in the samples. Sputum will be processed within 2 hours of collection. The selected sputum plugs should be as far as possible without saliva, processed into a weighed Eppendorf tube and processed with 4x weight/volume of 0.1% Dithiothreitol. Afterwards 2x weight/volume of Phosphate-buffered saline (PBS) was added. Samples will be filtered through 48 µm mesh and centrifuged for 10 minutes at 790 x g to remove the cells. Supernatants will

be stored at -80C° until further analysis with Cytometric Bead Array (CBA) as described (26).

### **Sputum cells**

Specimens containing levels of squamous epithelial cells less than 10% of the total inflammatory cell number will be considered adequate. At least 400 inflammatory cells will be microscopically counted for each specimen. Neutrophils, eosinophils, lymphocytes, basophils and macrophages will be expressed as percentages of the total cell count.

### **Cytometric bead array**

For analyses of sputum and cell culture supernatants we will use the sandwich-ELISA based technique of Cytometric Bead Array (CBA) to detect different pro-inflammatory cytokines or chemokines according to the manufacturer's protocol. Concentrations of cytokines/chemokines will be determined in sputum samples or cell culture supernatants using the BD™ CBA Flex Set System for the measurement of IL-1, IL-6, IL-8, INF- $\gamma$ , TNF- $\alpha$  and MCP-1, respectively. (BD Bioscience-PharMingen, San Diego, CA, USA) (26).

## **8 ADVERSE EVENTS**

### **8.1. DEFINITION 1**

**Adverse Event (AE):** an adverse event (AE) is any untoward medical occurrence in a patient or clinical trial subject administered a medicinal product and which does not necessarily have a causal relationship with this treatment. An adverse event can therefore be any unfavorable and unintended sign (including abnormal laboratory findings), symptom, or disease temporally associated with the use of an investigational medicinal product, whether or not considered related to the investigational medicinal product.

**Adverse Drug Reaction (ADR):** an adverse drug reaction is a response to a medicinal product, which is noxious and unintended and which occurs at doses normally used in man for the prophylaxis, diagnosis or therapy of disease or for the restoration, correction or modification of physiological function (article 1(11) of Directive 2001/83/EC).

All adverse events judged by either the reporting investigator or the sponsor as having a reasonable causal relationship to a medicinal product is qualified as adverse drug reactions. The expression reasonable causal relationship means to convey in general that there is evidence or argument to suggest a causal relationship.

**Unexpected adverse event (UAE):** an unexpected adverse event is an adverse event with the investigational product not previously reported (in nature, severity or incidence) and not consistent with the applicable product information (e.g. Investigator's Brochure for an unapproved investigational product or Summary of Product Characteristics (SPC) for an authorized product). If there are reasonable grounds for the suspicion that the UAE is causally related to the trial drug, it must be considered as ADR.

- When the outcome of the adverse event is not consistent with the applicable product information this adverse reaction should be considered as unexpected.
- Severity: the term "severe" is often used to describe the intensity (severity) of a specific event. This is not the same as "serious," which is based on patient/event outcome or action criteria.

The adverse events intensity is classified using the following definitions:

- Mild: The adverse event is transient, requires no treatment, and does not interfere with the study's subject daily activities.
- Moderate: The adverse event introduces a low level of inconvenience or concern to the study subject and may interfere with daily activities, but is usually ameliorated by simple therapeutic measures.
- Severe: The adverse event interrupts the study subject's usual daily activity and requires systematic therapy or other treatment.

## 8.2. DEFINITION 2

**Serious Adverse events:** An adverse event (AE) is defined as serious whenever the outcome is:

- a. death
- b. requiring inpatient hospitalisation or prolongation of existing hospitalisation
- c. resulting in persistent or significant disability / incapacity
- d. life-threatening

e. involving malignancy or congenital anomaly.

*Medical judgement should be exercised in deciding whether an adverse event/ reaction is serious in other situations. Important adverse events/ reactions that are not immediately life-threatening or do not result in death or hospitalisation but may jeopardise the patient or may require intervention to prevent one of the other outcomes listed in the definition above, should also be considered serious.*

Starting from Visit 2, and for all subsequent examinations during the trial, all symptoms or diseases which were not present at the initial examination (Visit 1) must be recorded. Documentation regarding the adverse event should be made as to the nature, date of onset, end date, seriousness, severity, course, relation to trial medications, action(s) taken and outcome of any signs or symptoms observed by the physician or reported by the patient upon indirect questioning or recorded on a diary card. In any case the patient has to be followed carefully until the adverse event has resolved or at least stabilised. If there is a worsening of a medical condition that was present before starting the trial, this should be considered as an adverse event and a complete evaluation should be recorded. The trial medications relationship to each adverse event should be determined by the investigator based on the following definition:

### 8.3. DEFINITION 3

- **Certain:** A clinical event, including laboratory test abnormality, occurring in a plausible time relationship to drug administration, and which cannot be explained by concurrent disease or other drugs or chemicals. The event must be plausible pharmacologically or phenomenologically, and its clinical response to withdrawal of the drug (dechallenge) should be clinically plausible. It must also be confirmed by a satisfactory challenge procedure.

NOTE: The decision to perform a formal rechallenge must be made by the Investigator and the Clinical Project Manager after reviewing the patient's complete history.

- **Probable:** A clinical event, including laboratory test abnormality, with a reasonable time sequence to drug administration, unlikely to be attributed to concurrent disease or other drugs or chemicals, and which follows a clinical plausible response on withdrawal (dechallenge). Rechallenge information is not required to fulfil this definition.

- 
- **Possible:** A clinical event, including laboratory test abnormality, with a reasonable time sequence to administration of the drug, but which could also be explained by concurrent disease or other drugs or chemicals. Information on drug withdrawal may be lacking or unclear.
  - **Unlikely:** A clinical event, including laboratory test abnormality, with temporal relationship to drug administration which makes a causal relationship improbable, and in which other drugs, chemicals or underlying disease provide more plausible explanations.
  - **Unassessable:** A report suggesting an adverse drug reaction, which cannot be judged because information is insufficient or contradictory, and which cannot be supplemented or verified.
  - **Not related:** An adverse event, which is definitely not related causally to drug administration.

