| Inclusion/ Exclusion                          | X                                  |                   |                   |                            |                   |                    |
| Physical Examination Vital Signs              | X                                  | X                 | X                 | X                          | X                 | X                  |
| Lung function (Bodyplethys.)                  | X                                  | X                 | X                 | X                          | X                 | X                  |
| Post Reversibility Lung function              | X                                  | X                 | X                 | X                          | X                 | X                  |
| Urine Pregnancy testing           | X                                  | X                 | X                 | X                          | X                 | X                  |
| Laboratory examinations           | X                                  |                   |                   |                            |                   |                    |
| COPD Assessment Test (CAT) handover           | X                                  | X                 | X                 | X                          | X                 | X                  |
| Collection and Review of BDI / TDI St George  | X                                  |                   | X                 |                            | X                 | X                  |

---

|                                            |   |   |   |   |   |   |
|--------------------------------------------|---|---|---|---|---|---|
| Inhalation of medication                   | X | X | X | X | X | X |
| Lung function after Sputum collection      | X | X | X | X | X | X |
| Monitoring Ease of expectoration           | X | x | x | x | x | x |
| Nebulizer and Drug dispensation            | X |   |   | X |   |   |
| Collection of trial drug/ Compliance check | x | x | X | x | x | X |
| Recording of Adverse Events                |   | X | X | X | X | X |
| Appointment for the next visit             | X | X | X | X | X |   |

1) If applicabel

2) Laboratory examinations : Hematology Makrophagen Activation test

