## 1.2. TOLARANCE OF TYLAXOPOL

Side-effects in the form of hypersensitivity reactions have only occurred very rarely. Nausea has occasionally occurred in allergic subjects. Occasionally, the first deep breaths may be followed by an initial urge to cough, which immediately disappears after moistening of the mucous membrane.

Hutschenreuter administered more than 1000 individual inhalations of Tacholiquin ® to 106 surgical patients. In doing so, he showed that Tacholiquin ® was very well tolerated by the patients. There were also no signs of intolerance in patients who inhaled tyloxapol several times a day over a period of 9 weeks (9).

In various studies, patients were treated continuously with tyloxapol for up to 4 years (in one case, it was administered in an aerosol tent every night for 4 years) with no side-effects being observed (10, 17, 22).

Segal et al (23) administered Tacholiquin ® continuously over 24 hours per day to children and adults with pertussis over a period of 7 days, and observed no side-effects (23).

Farber et al. (20) pointed out that tyloxapol is harmless, safe and effective in the treatment of patients with bronchiectases. According to the authors, tyloxapol facilitates the expectoration of sputum. In particular, the authors pointed out that tyloxapol caused no serious side-effects and is an ideal carrier for antibiotics, bronchodilators and substances with a vasoconstrictive action as a result of its chemical structure.

Camarata et al. (24) also established no adverse drug reactions after this active substance was administered to patients with atelectases.

There are no known interactions with other drugs.

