#### 6.1.1. RECRUITMENT PROCEDURE

At Visit 1 before any assessment necessary for the study, the COPD patient will be informed by the physician according to the “Patient information” sheet. The patient will then give a written consent by signing the Patient Consent. As soon as the specific inclusion and exclusion criteria at Visit 1 have been checked, eligible patients will be assigned a randomization number in ascending order. They will then start double-blind trial treatment.

Additional visits can be scheduled and performed according to the investigators judgment of how to best manage the patient. At these visits in addition to recording any SAEs, AEs and concomitant medication use, a physical examination, vital sign assessment and lung function tests are to be performed.

Any unscheduled visits are to be recorded in the other clinical visits CRFs.

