### 6.2. **PROCEDURE BY VISIT**

#### 6.2.1. **METHODS AND MEASUREMENTS**

##### **Visit procedures at screening visit and before treatment phase A (Visit 1)**

- Patient information/Informed consent
- Date of visit
- Demographic data,
- Medical history and concomitant diseases
- Physical examination / Vital signs
- Concomitant medications
- Bodyplethysmography
- Bronchodilator response to Salbutamol
- Completing Questionnaires (CAT, BDI, St George)
- Inclusion/exclusion criteria

- Randomisation and drug dispensation
- Laboratory examination (including Urinalysis)
- Inhalation of blinded medication by nebuliser
- Sputum collection
- Recording side effects
- Recording “ease of expectoration”.
- Lung function monitoring up to one hour after sputum collection
- Lung clearance index one hour after inhalation
- Dairy explanation
- Appointment for the next visit

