#### 8.4. REPORTING AND RECORDING OF ADVERSE EVENTS

All symptoms or diseases observed by the physician or reported by the volunteer upon indirect questioning and which were not present at the initial examination (Visit 1) must be recorded as an adverse event.

Documentation regarding the adverse event should be made as to the nature, date of onset, end date, seriousness, severity, rate of appearance, corrective therapy, relation to trial medication, action(s) taken and outcome of any signs and symptoms. In any case, the volunteer has to be followed carefully until the adverse event has resolved or at least stabilized. If there is a worsening of a medical condition that was present before starting the trial, this should be considered as an adverse event and a complete evaluation should be recorded.

The trial medications relationship to each adverse event should be determined by the investigator based on the definitions detailed above.

All information regarding adverse events must be recorded in the specific AE pages of the CRF.

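### The protocol contradicts itself on whether reactions to the first blinded inhalation, taken at Visit 1, are recorded as adverse events

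*Protocol*

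**What the plan says.** **Dosing.** Section 6.1.1 has patients randomised at Visit 1 once eligibility is checked: "They will then start double-blind trial treatment". The Visit 1 list in section 6.2.1 includes "Inhalation of blinded medication by nebuliser", followed by sputum collection and lung-function monitoring.

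**AE recording that leaves out Visit 1.**
- Section 8.2 sets the scope of recording: "Starting from Visit 2, and for all subsequent examinations during the trial, all symptoms or diseases which were not present at the initial examination". The examination meant is that of Visit 1.
- Flow chart: the row "Recording of Adverse Events" is blank at Visit 1 and marked at Visits 2 to 6.

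**AE recording that could include Visit 1.**
- The Visit 1 list contains "Recording side effects" after the inhalation.
- Section 8.4 covers all symptoms or diseases "which were not present at the initial examination (Visit 1) must be recorded as an adverse event", with no Visit 2 start. It sends all AE information to the AE pages of the CRF.
- Section 8.2 adds: "If there is a worsening of a medical condition that was present before starting the trial, this should be considered as an adverse event".
- A diary is explained at Visit 1, filled in daily for AEs (section 6.2.2) and checked at each visit (section 5.8).

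**Use of the data.** Section 9.6 rests the safety assessment chiefly on how often AEs occur.

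**The concern.** Visit 1 serves both as the reference for what counts as a new symptom and as the day of first exposure. Unless the reference is fixed as pre-dose, a reaction to that day's inhalation can be read as already present at Visit 1 and so not new. Section 8.2 and the flow chart then add a second barrier by starting the record at Visit 2.

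The protocol's own tolerability text (section 1.2) shows the kind of event at issue: "Occasionally, the first deep breaths may be followed by an initial urge to cough", which it says passes at once. Such an event leaves nothing to find a week later. Since safety rests on AE frequency, staff need a single answer on whether each patient's first exposure is inside the AE record. An analysis plan cannot recover events that were never written down.

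**Working it through.** No figure in the protocol is at stake. The check is a comparison of the passages, with arithmetic only to bound the size.

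**1. Flow chart against visit lists (section 6.2.1)**

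| Visit | Blinded inhalation | AE row in flow chart | Side-effects item in list | Separate AE item in list |
|---|---|---|---|---|
| 1 (first dose, phase A) | yes | blank | yes | no |
| 2 | yes | marked | yes | yes |
| 3 | yes | marked | yes | no |
| 4 (first dose, phase B) | yes | marked | yes | no |
| 5 | yes | marked | yes | yes |
| 6 | yes | marked | yes | no |

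The lists for Visits 1 and 4 have the same safety item, yet the flow chart marks AEs at Visit 4 only. Visits 2 and 5 list side effects and AEs separately, as if they differed. Visits 3, 4 and 6 list only side effects although the chart marks AEs there, as if they were the same. The protocol never says which holds.

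**2. Section 8.2 against section 8.4.** Both use the initial examination at Visit 1 as reference. Section 8.2 starts at Visit 2 and section 8.4 does not. Neither says whether the examination is before or after the inhalation.

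**3. Upper limit on the loss.** Inputs: 24 patients, including 4 expected drop-outs (section 3), and two phases. Assumption: nothing from Visit 1 reaches the AE record.
- All 24 reach phase B: first doses = 24 × 2 = 48; uncounted = 24/48 = 50%.
- All 4 drop-outs leave before Visit 4: first doses = 24 + 20 = 44; uncounted = 24/44 = 54.5%.

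**4. What that limit would mean for tyloxapol.** Further assumption: a 1:1 split between sequences, which the protocol does not state. Then 12 of 24 first tyloxapol doses are counted (10 of 20 among evaluable patients), and likewise for saline.

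With zero reactions seen, the one-sided 95% upper bound on the reaction rate is 1 − 0.05^(1/n):
- n = 24: 11.7%; n = 12: 22.1%
- n = 20: 13.9%; n = 10: 25.9%

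The chance of seeing at least one reaction is 1 − (1 − p)^n, for assumed true rates p:

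| p | n = 24 | n = 12 |
|---|---|---|
| 5% | 71% | 46% |
| 10% | 92% | 72% |
| 20% | 99.5% | 93% |

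**The case against.** A reader might infer that period 1 first-dose reactions are simply lost and that the AE comparison between products is distorted. The documents do not support either claim, for these reasons:

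- The rule refers to an examination, and the Visit 1 list puts the physical examination before randomisation and inhalation. On that reading a reaction after dosing was not present and is an AE.
- Section 8.4, the section devoted to AE recording, has no Visit 2 start.
- The Visit 2 start in section 8.2 can be read as when events are written down, not as a cut-off for onset. The section asks for onset dates and admits diary entries.
- At Visits 3, 4 and 6 the side-effects item appears to serve as the AE item, so it may do so at Visit 1.
- Many of these patients cough at baseline, and a worsened cough could count under the worsening clause.
- Section 8.5 requires serious events to be reported within 24 hours, whatever the visit.
- The gap is by period. With balanced sequences it lowers both products' counts about equally, and section 9.6 specifies no formal between-treatment AE test.
- Section 1.2 does not confine the cough to the first-ever dose, and inhalation is three times daily.

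Most of this stands. It rules out total loss as the expected result, and it rules out bias towards one product.

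It does not remove the contradiction. The order of the Visit 1 list is weak evidence for a pre-dose reference: the list places laboratory tests after randomisation, although exclusion criterion 9 uses haematology and urinalysis from that visit. The diary may miss a reaction that starts and ends in the clinic. The worsening clause covers conditions present before the trial, not a new symptom. Nothing links the Visit 1 side-effects entry to the AE pages of the CRF.

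**Conclusion.** The point holds as an internal contradiction. Section 8.2 and the flow chart leave Visit 1 out of AE recording. The Visit 1 list and section 8.4 can be read as including it, and the reference examination is not tied to the time of dosing. Short-lived, non-serious reactions to the first inhalation of period 1 may be missed or under-counted relative to period 2.

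The loss cannot be estimated from the protocol, because it depends on how the site reads these passages. About half of first-dose exposures (50%, or up to 54.5% with early drop-out) is the ceiling, reached only if nothing from Visit 1 is captured. A site that treats side effects as AEs would lose little or nothing. With balanced sequences the result would be understated first-dose rates for both products, not an advantage for one. Serious events are not affected.

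This is a modest point, but worth correcting before recruitment because the omission could not be repaired afterwards.

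**What to change.** Reconcile section 8.2, section 8.4, the flow chart and the visit lists:

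1. In section 8.2, replace the Visit 2 start with recording from the first inhalation at Visit 1.
2. In sections 8.2 and 8.4, define the reference as the Visit 1 examination before the first inhalation.
3. Mark Visit 1 in the AE row of the flow chart.
4. State that side-effect entries at every visit go to the AE pages of the CRF, and use one term for the item in all six lists.

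The cost is a few sentences, one flow-chart cell and an AE page available at Visit 1. No visit, procedure or patient is added.
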